## Abstract

**ABSTRACT:**

**Introduction:**

Established personal and familial risk factors contribute collectively to a woman’s risk of breast or ovarian cancer. Existing clinical services offer genetic testing for pathogenic variants in high-risk genes to investigate these risks but recent information on the role of common genomic variants, in the form of a Polygenic Risk Score (PRS), has provided the potential to further personalise breast and ovarian cancer risk assessment. Data from cohort studies support the potential of an integrated risk assessment to improve targeted risk management but experience of this approach in clinical practice is limited.

**Methods and analysis:**

The polygenic risk modification trial is an Australian multicentre prospective randomised controlled trial of integrated risk assessment including personal and family risk factors with inclusion of breast and ovarian PRS vs standard care. The study will enrol women, unaffected by cancer, undergoing predictive testing at a familial cancer clinic for a pathogenic variant in a known breast cancer (BC) or ovarian cancer (OC) predisposition gene (*BRCA1*, *BRCA2*, *PALB2*, *CHEK2*, *ATM*, *RAD51C*, *RAD51D*). Array-based genotyping will be used to generate breast cancer (313 SNP) and ovarian cancer (36 SNP) PRS. A suite of materials has been developed for the trial including an online portal for patient consent and questionnaires, and a clinician education programme to train healthcare providers in the use of integrated risk assessment. Long-term follow-up will evaluate differences in the assessed risk and management advice, patient risk management intentions and adherence, patient-reported experience and outcomes, and the health service implications of personalised risk assessment.

**Ethics and dissemination:**

This study has been approved by the Human Research Ethics Committee of Peter MacCallum Cancer Centre and at all participating centres. Study findings will be disseminated via peer-reviewed publications and conference presentations, and directly to participants.

**Trial registration number:**

ACTRN12621000009819.

Strengths and limitations of this studyThe trial is an Australian nationwide, multicentre randomised controlled trial that will generate high-level evidence on the clinical, psychosocial and health implications of integrated breast and ovarian cancer risk assessment in clinical practice.Participants will be enrolled following referral for clinical predictive genetic testing, allowing study activities to be integrated with existing clinical processes, and include both individuals who test positive and negative for a pathogenic variant.A limitation is that the breast and ovarian cancer Polygenic Risk Score employed in the trial were developed in European populations and are expected to be less predictive for many women in the ancestrally diverse Australian population, requiring additional adjustment to account for this effect.

## Introduction

 The hereditary component underlying breast and ovarian cancer risk is one of the highest for any solid tumour, meaning that women at highest risk can be identified through genetic testing combined with personal and family risk factors, using validated risk assessment tools.^1 2^ A highly effective way to prevent breast cancer deaths is to target risk management strategies to those at higher risk. At the high end of familial risk, genetic testing is well-established for rare pathogenic variants (PVs) in a panel of breast cancer genes.^3^ The best known are *BRCA1* and *BRCA2* which convey average lifetime breast cancer risks of 50% to 70% and significant risks for ovarian cancer and other malignancies.^4^

For women who carry a PV in *BRCA1* or *BRCA2,* evidence shows that risk management options, including screening from a young age, breast MRI screening, risk-reducing medication and prophylactic mastectomy and oophorectomy, are effective.^5^ The current panel of genes with strong evidence for use in clinical practice include *PALB2, CHEK2*, *ATM*, *RAD51C* and *RAD51D* with additional genes such as *BARD1* (breast cancer) and *BRIP1* (ovarian cancer) continuing to emerge. Notably, with the exception of *PALB2*,^6^ the breast cancer risk for these more recently described genes is substantially lower than for *BRCA1* and *BRCA2* and they are commonly described as moderate risk genes (risks twofold to fourfold compared with the population). The clinical model developed over years to manage the clear high risks of *BRCA1* and *BRCA2* has had to adapt to the complexity introduced by greater clinical uncertainty from both the less mature evidence and the more moderate risks associated with the recently identified genes. However, genetic testing, including all of these genes, is now a standard part of breast cancer care.^7^

In parallel initiatives, hundreds of common single nucleotide variations or polymorphisms (SNPs) in the genome have been identified from large genome-wide association studies, each of which is associated with a small risk of breast cancer.^8^,^10^ When combined into a single measure, known as a Polygenic Risk Score (PRS), this information can be used to describe the distribution of breast cancer risk in the general population^8^ and in familial breast cancer.^11^ In contrast to rare variants, PRS can be applied to all women. The magnitude of risk for different levels of polygenic risk has been established in large studies^12^ and validated prospectively.^13^

Initial studies that examined the effect of a PRS on breast cancer risk in *BRCA1* and *BRCA2* carriers showed the absolute lifetime risk of breast cancer was around 10%–20% greater for carriers in the highest decile of the PRS distribution compared with the lowest.^14^ These effects have been further examined for breast and ovarian cancer with expanded PRS: 313 SNPs for breast^8^ and 36 SNPs for ovarian cancer.^15^ Potentially, even more significant variation has been demonstrated with the combination of the PRS and moderate-risk genes such as *CHEK2*. A study of 844 carriers of a *CHEK2* PV found an average lifetime breast cancer risk close to the population level (14.3%) in the 20% of carriers with the lowest PRS and a high risk (32.6% lifetime risk) in the same proportion of women with the highest PRS.^16^

The psychological outcomes of germline genetic testing for *BRCA1* and *BRCA2* are well understood. Studies show little evidence of negative impacts in the longer term in those carrying a PV, and some benefits for those found to be non-carriers.^17^,^20^ Women’s responses and understanding of polygenic breast cancer risk information (the PRS) are less well researched. A long-term Australian study (the ViP study) examining the role of the PRS in clinical risk assessment^11^ showed a high level of comprehension and acceptance of receiving such information^21^,^23^ and has informed the patient care model for the current trial.

Continuing concerns about the use of PRS information include its use in non-European populations.^24^ The most widely researched PRS was developed using data from women of European background and are both less well characterised and, where examined, are less predictive in women of all other ancestral backgrounds.^25^ In addition, there are concerns that the PRS effects are only moderate, requiring a different conceptual model for PRS-based risk assessment compared with single gene approaches. A recent review of the role of PRS in clinical care concluded that there is not yet unequivocal evidence of demonstrated clinical benefit in any setting^26^ and more clinical data is needed before PRS is ready for routine implementation for breast cancer risk assessment.^27^ Large well-designed randomised controlled trials (RCTs) are needed to assess outcomes such as the accuracy of PRS-informed risk assessments and their effect on risk-reducing strategies and breast cancer incidence, acceptability and understanding of PRS information, and the psychological and health system impacts.

Currently, thousands of women attend familial cancer clinics (FCCs) annually across Australia to be tested for a PV in a high-risk or moderate-risk gene found in their family as a cause for breast (±ovarian) cancer. These women represent an important potential study group for an initial examination of the clinical value of PRS risk modification as they are already undergoing predictive genetic testing, allowing the study to be integrated with existing clinical processes. Here, we describe the polygenic risk modification (PRiMo) trial, an Australian multicentre prospective randomised controlled trial of integrated risk assessment including personal and family risk factors with inclusion of breast and ovarian PRS vs standard care. The protocol is based on the Standard Protocol Items: Recommendations for Interventional Trials (SPIRIT) recommendations,^28^ and a completed SPIRIT checklist is available (see online supplemental file).

## Methods and analysis

### Aims

The primary aim of the trial is to compare the performance of an integrated assessment of breast and ovarian cancer risk that incorporates PRS risk modification, along with personal and familial risk factors, with the current standard of care in a cohort of Australian women undergoing predictive genetic testing for a breast/ovarian cancer gene at an FCC. In the short term, the study will compare the distribution of assessed risk, and risk management recommendations and intentions in the PRiMo intervention group vs the standard care group. In the medium to long term, the study will (i) assess uptake and adherence to risk management strategies and (ii) use follow-up of prospective cancer events to examine the accuracy and calibration of the risk assessment between the PRiMo risk assessment and standard care.

Secondary aims are to assess patient attitudes and experience when undergoing personalised genomic risk assessment for breast and ovarian cancer and to establish the health service implications of implementing PRS-risk-modified assessments in clinical practice including a health economic evaluation.

### Design and setting

The PRiMo intervention is being evaluated using a two-arm superiority multicentre RCT. Study participants will be recruited through 11 dedicated FCCs around Australia where unaffected women are referred for predictive genetic testing of high-risk or moderate-risk breast or ovarian cancer genes, following detection of a likely pathogenic (class 4) or pathogenic (class 5) variant in a family member. Participants in the RCT are allocated to either (i) a standard care group, who undergo predictive testing as per the FCC’s usual practice or (ii) an intervention group, where the genetic healthcare provider (GHP) at their FCC provides them with risk assessment and management advice based on the PRiMo risk assessment, which integrates their rare PV genetic test result, breast and ovarian cancer PRS, detailed family history information and personal risk factors. Based on consumer input the study design allows participants in the standard care group to crossover and receive their PRiMo risk assessment including the PRS, 1 year after their standard results appointment so that this is eventually available to all participants.

Although comparatively rare, PVs in breast cancer predisposition genes other than *BRCA1* and *BRCA2* are of particular interest given that in this context, the PRS results can have increased implications for risk stratification. To ensure adequate representation of these genes, the study will also recruit a retrospective cohort of women who have previously been found to carry a PV in one of these genes. These participants will be provided with updated risk management advice from a GHP at their FCC based on the PRiMo risk assessment.

The study opened at the first site in July 2021 and is expected to take at least 5 years including recruitment and follow-up. Figure 1 summarises the study procedures for the prospective RCT and the retrospective cohort.

**Figure 1 F1:**
[figure not shown]
Study procedures flowchart. APPT, appointment; FCC, Familial Cancer Centre; PRS, Polygenic Risk Score; PV, pathogenic variant.

### Intervention

Standard care at participating FCCs currently provides risk assessment and risk management advice based on the result of the predictive gene test, along with basic risk factor information based on the national guidelines on cancer risk management for gene carriers.^29^ Where additional personal risk factor information is included, the risk is typically incorporated using the CanRisk tool—a validated online tool to calculate an integrated lifetime breast and ovarian cancer risk.^1 30^ This tool has been shown to be acceptable to clinicians in the genetics setting,^31^ although its use in clinical practice in Australian FCCs was variable at the time the trial commenced. The CanRisk tool is supported by grant PPRPGM-Nov20\100 002 from Cancer Research UK.

The PRiMo intervention is an enhanced breast cancer risk assessment that combines PRS calculated from a combination of common genomic variants with the result of a predictive genetic test and a standard set of basic risk factor information (age, lifestyle risk factors and family history of cancer). This personalised risk assessment is calculated using the CanRisk tool and the output summarised in a custom report that includes the primary genetic information and a risk summary of 5-year, 10-year and lifetime risks for breast and ovarian cancers. In both arms, risk management advice, ongoing follow-up and clinical care will be determined by the participant’s managing FCC and medical team. The retrospective cohort participants have previously tested positive for a moderate-risk gene and had a ‘standard care’ results appointment. Consenting participants in this group will all receive a PRiMo risk assessment and the analysis of the primary study aims will involve comparison of pre-result and post-result questionnaire data for the same women.

The use of PRS in an integrated individualised risk assessment is a novel element in clinical practice. To ensure that clinicians feel confident, and the study intervention is delivered in a standard manner, the trial included development of an education and training programme used with GHPs at participating sites. The programme comprises online learning covering the theoretical aspects of PRS and a facilitated virtual workshop with pre-recorded roleplays and case discussions.^32^

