#### Retrospective cohort

To ensure adequate representation of the rarer genes, the trial is inviting up to 400 women who have previously tested positive for a PV in *PALB2, CHEK2, ATM*, *RAD51C* or *RAD51D*. Other inclusion and exclusion criteria are as for the prospective RCT.

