### Randomisation

Randomisation occurs following completion of the pre-test counselling appointment and pre-result baseline questionnaire. Participants in the prospective RCT are randomly assigned to either standard care or PRiMo intervention with a 1:1 allocation as per a computer-generated simple randomisation schedule using the REDCap randomisation module. The trial staff allocating participants do not have access to the randomisation schedule.

To minimise discrepancies in risk advice provided to relatives managed by the same FCC, only the first participant in a family at that site will be randomly assigned to either standard care or intervention. Any related participants that attend the same FCC will be allocated to the same group. Participants will not be informed of this procedure and potential participants will not be aware of their group prior to enrolment.

Given the nature of the intervention, participant and clinician blinding is not possible and both the participant and their FCC will be informed of the outcome following allocation, and procedures for unblinding are not required. Analysis of the primary study aims will be performed without knowledge of the intervention status of each group.

Participants in the retrospective cohort will not be randomised and all will receive the intervention.

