### Data analysis

Figure 3 shows the between-group (RCT) and within-group (retrospective cohort) comparisons for the outcome measures.

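### The retrospective cohort's before-and-after comparison has no control, so it cannot answer the primary aim (PRiMo versus standard care) for the rarer genes

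*Protocol article*

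**What the plan says.** The Aims section sets the primary aim as a comparison of the integrated PRiMo assessment "with the current standard of care in a cohort of Australian women undergoing predictive genetic testing". Design and setting describes a two-arm superiority randomised trial for this purpose.

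A second, retrospective cohort is added so that the non-BRCA genes are adequately represented, because the PRS may matter more for risk stratification there. Under Sample, "the trial is inviting up to 400 women who have previously tested positive for a PV in" PALB2, CHEK2, ATM, RAD51C or RAD51D. On allocation, the Randomisation section says: "Participants in the retrospective cohort will not be randomised and all will receive the intervention".

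The Intervention section describes the history of these women: "The retrospective cohort participants have previously tested positive for a moderate-risk gene and had a ‘standard care’ results appointment". It then fixes their analysis: "the analysis of the primary study aims will involve comparison of pre-result and post-result questionnaire data for the same women". Data analysis confirms the split: "Figure 3 shows the between-group (RCT) and within-group (retrospective cohort) comparisons for the outcome measures". On what the cohort receives, Design and setting says: "These participants will be provided with updated risk management advice from a GHP at their FCC based on the PRiMo risk assessment".

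**The concern.** The primary aim is a contrast between two forms of care. In this cohort only one form is given, and the planned contrast is between two dates in the same women. The change from pre-result to post-result is the effect of PRiMo plus the effect of everything else that happens between the two questionnaires. Here that includes being approached by the clinic again and attending a second results appointment at which the advice is brought up to date. A repeat appointment under ordinary care might also change risk perception, worry or quality of life.

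At stake is what the trial can say about the rarer genes. The cohort was added to strengthen the evidence for them, and it may supply much of it. Because the article ties the before-and-after comparison to the primary aims, a significant change could be taken as evidence on PRiMo versus standard care when the design cannot show that.

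**Working it through.** **Setting the sections side by side**

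1. Estimand: PRiMo versus standard care (Aims).
2. Cohort data: PRiMo only, no randomisation (Randomisation).
3. Cohort contrast: post-result against pre-result in the same women (Intervention; Data analysis).
4. The article describes no concurrent control and no adjustment for time for this cohort.

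Write the mean within-woman change as Δ = θ + β. Here θ is the PRiMo effect relative to standard care, and β is the change that re-contact and a new standard-care appointment would have produced. The cohort estimates Δ only. Without a group that shows β, θ is not identified, whatever the sample size and whichever items are collected.

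**What belongs in β**

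- *Re-contact and a new appointment with updated advice.* This is the main threat, and the article itself says that the advice is updated. The Introduction calls the evidence on the newer genes less mature, so ordinary advice may also have moved since a woman's first appointment. On CanRisk, the Intervention section adds "although its use in clinical practice in Australian FCCs was variable at the time the trial commenced", so the earlier care was not uniform.
- *Ageing.* This is minor. Pre-result questionnaires are completed before the PRiMo results appointment, and the first post-result reading is at 1 month (Table 1).
- *Pedigree and personal risk factors.* These do not belong in β. The article defines them as components of PRiMo.

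**Illustration of size**

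The article gives no effect size, alpha or power for this cohort, so there is no figure to reproduce. All inputs below are assumptions except the ceiling of 400 women: θ = 0, pre-level 50%, drift d = 5 points, within-woman correlation ρ = 0.5, McNemar test, two-sided 0.05. The second size, n = 200, represents half of the ceiling.

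- P(yes at both times) = 0.50 × 0.55 + 0.5 × √(0.25 × 0.2475) = 0.275 + 0.1244 = 0.3994.
- Discordant cells: 0.50 − 0.3994 = 0.1006 and 0.55 − 0.3994 = 0.1506. Their sum is ψ = 0.2513.
- Rejection ≈ Φ[(d√n − 1.96√ψ) / √(ψ − d²)], with the opposite tail negligible.
- n = 200: (0.7071 − 0.9824) / 0.4988 = −0.552, which gives 29%.
- n = 400: (1.0000 − 0.9824) / 0.4988 = 0.035, which gives 51%. Simulation gives 52%.

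Other values, from simulation at ρ = 0.5 unless stated:

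| Drift | n = 200 | n = 400 |
|---|---|---|
| 0 points | 5% | 5% |
| 3 points | 14% | 23% |
| 5 points | 29% | 52% |
| 5 points, ρ from 0.3 to 0.7 | 22–45% | 39–74% |
| 10 points | 81% | 98% |

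A second calculation assumed ψ directly, from 0.10 to 0.30. With 5-point drift it gives 25–61% for 200 pairs and 45–89% for 400. With 2-point drift and 400 pairs it gives 11–24%.

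For a score with drift 0.1 SD and ρ = 0.5, z = 0.1 / √(2 × 0.5 / n). This is 1.41 for n = 200 and 2.00 for n = 400, giving 29% and 52%.

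**The case against.** The best defence is that the article already keeps the two parts apart. Superiority is assessed in the randomised trial, alpha and power are set for the arms and their subgroups, and the cohort is analysed within group and not pooled. A reader might infer that any change in the cohort will be counted as a PRiMo effect. No sentence says so, and that stronger reading is not supported. What remains is that the Intervention section names the comparison as the analysis of the primary aims, and those aims are comparative.

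Other objections also stand in part:

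- PRiMo is a package, so the absence of a PRS effect is not the right null for the primary aim. A CanRisk run without the PRS is not standard care either. A with/without-PRS contrast therefore answers a narrower question and must be labelled so.
- Standard-care carriers in the randomised trial would be a poor control for drift. They learn of a positive result for the first time, while the cohort already knows its result.
- The rejection rates rest on assumed drift, and 400 is a ceiling on invitations. They illustrate the problem and do not predict an error rate.
- The psychosocial model includes other stressful life events. That handles one source of background change, but not the effect of the appointment itself.
- Figure 3 and the full protocol are not shown and may add detail on interpretation. They could not supply the control that an all-treated cohort lacks.

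Table 1 lists no pre-result reading of risk management intentions or uptake. That is a separate matter, and adding those items would still leave the comparison uncontrolled.

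**Conclusion.** The point holds in a limited form. The planned before-and-after comparison in the retrospective cohort cannot separate PRiMo from re-contact and a new appointment with updated advice, so it cannot answer the primary aim for PALB2, CHEK2, ATM, RAD51C and RAD51D. This follows from the design and needs no assumption. The randomised comparison is untouched.

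The size of any false-positive risk is unknown, because the article gives no basis for background change. Under the assumptions shown, a 5-point drift would bring a nominal 5% test to about 29% with 200 women and 52% with 400, and with no drift it stays at 5%. The change should be made because it alters what can be concluded for these genes at little cost. It does not threaten the trial's main result.

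**What to change.** Amend the Intervention section, and Data analysis to match:

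1. Draw conclusions on PRiMo versus standard care only from the randomised arms, including their carriers of non-BRCA variants.
2. Report the retrospective cohort's pre/post questionnaire changes separately, as descriptive estimates with confidence intervals, and do not attribute them to PRiMo.
3. For assessed risk in this cohort, add a contrast within the same woman on the same date: her CanRisk category with the PRS against her category without it, from the pedigree, risk factors and gene result already held. Label it as the incremental contribution of the PRS, not as PRiMo versus standard care.
4. Do not use standard-care carriers from the randomised trial as a control for drift.

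The cost is a change of wording and one extra CanRisk run per woman, with no new visits or participants. The downside is a more modest claim from the cohort. Comparative evidence for the rarer genes will then rest on however many such carriers are randomised, a number the article does not give.
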